### 2.4. Experimental Protocol

This study will employ a repeated-measures within-subject design to evaluate the propulsion efficiency and biomechanical characteristics of a detachable push–pull dual-propulsion device developed for manual wheelchair users. The experiment will be conducted in a controlled laboratory setting at the National Rehabilitation Center, where each participant will perform two propulsion conditions: (1) forward (push) propulsion and (2) backward (pull) propulsion. Each condition will be repeated five times, resulting in ten trials of propulsion per participant. The order of the conditions will be randomized for each individual to minimize potential learning or fatigue effects.

The experimental session will consist of several sequential phases, including informed consent, familiarization, propulsion trials (push and pull), rest periods, and MVC measurements. A structured participant timeline will be followed to ensure procedural consistency across subjects, as outlined in Table 1. Each propulsion condition will be completed five times over a 10-m track, with adequate rest provided between trials. After the propulsion trials, maximum voluntary contraction (MVC) values will be collected for EMG normalization.

The experiment will take place along a 10-m straight indoor track. Before data collection, participants will receive a 3-minute familiarization session with the wheelchair equipped with the dual-propulsion device. During this time, participants will be instructed on how to operate the device and perform the experimental tasks. Adequate rest periods will be ensured throughout the protocol to minimize muscular fatigue. Upon completion of all propulsion tasks, MVC measurements will be obtained for each targeted muscle group, with each MVC performed three times for three seconds per trial.

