### 2.5. Outcome Measures

The outcome measures of this study are designed to evaluate the biomechanical differences in upper limb function during two propulsion modes: forward (push) and backward (pull). These include both kinematic and muscle activation variables.

Kinematic variables comprise joint angles, range of motion (ROM), and stroke trajectories, with a particular focus on the shoulder and elbow during the propulsion cycle.

Muscle activity will be evaluated using surface electromyography (sEMG), focusing on activation intensity and timing of the upper limb muscles involved in propulsion. Normalized iEMG and RMS values will serve as the primary metrics for inter-condition comparison. All EMG data are normalized to MVC, which is measured post-trial.

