### 2.6. Procedures

Kinematic data will be collected using a VICON motion capture system (Oxford, UK) equipped with 10 fixed cameras. Reflective markers will be placed on anatomical landmarks of the shoulder, elbow, wrist, and hand to capture movement during each propulsion cycle. The recorded data will be processed with Visual 3D software (C-Motion, Germantown, MD, USA) to extract joint angles, ROM, and stroke trajectories. Sampling will be conducted at 100 Hz, and all signals will be low-pass filtered before analysis.

sEMG signals will be recorded using a Trigno Wireless EMG system (Delsys Inc., Natick, MA, USA) from ten upper limb muscles on the dominant side: anterior, middle, and posterior deltoid; biceps brachii; triceps brachii; pectoralis major; upper, middle, and lower trapezius; and latissimus dorsi. Surface electrodes will be positioned according to SENIAM guidelines, ensuring consistent and valid placement across participants. However, the SENIAM guidelines do not provide placement recommendations for the pectoralis major and latissimus dorsi muscles. For the pectoralis major, electrodes will be placed approximately one-third of the distance from the suprasternal notch to the anterior axillary line, following the method described by Król et al., (2007) [17]. For the latissimus dorsi, electrodes will be aligned parallel to the muscle fibers, approximately 4 cm below the inferior angle of the scapula, as validated in a previous study [18].

EMG signals will be sampled at 2000 Hz and processed through bandpass filtering (20–450 Hz), full-wave rectification, and smoothing using a root mean square (RMS) algorithm with a 100 ms moving window. Both integrated EMG (iEMG) and RMS values will be calculated to provide complementary insights: iEMG will reflect the cumulative muscle activity over time, while RMS will highlight instantaneous variations in muscle activation.

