Maximum voluntary contractions (MVCs) will be measured post-trial and will be used to normalize all EMG signals for comparability. Although MVCs are commonly performed before experimental tasks, in this study, they will be conducted after the propulsion trials to prevent anticipatory muscle activation or learning effects that may influence natural propulsion patterns. Participants will be given a sufficient rest period after the trials to mitigate any fatigue effects before performing MVCs. For each muscle, MVC signals will be collected in three separate trials, each lasting 5 s, with 1-min rest intervals between trials to avoid fatigue. Participants will be seated in their manual wheelchairs, with their trunks supported and their arms positioned as needed for each targeted muscle. Verbal encouragement will be provided during each trial to help participants exert their maximum effort.

-For the deltoid (anterior, middle, posterior), participants will perform isometric shoulder flexion, abduction, and horizontal extension against resistance, respectively.-For the biceps brachii and triceps brachii, MVCs will be obtained during elbow flexion and extension against manual resistance at a 90° elbow angle.-For the pectoralis major, MVC will be performed via horizontal adduction against resistance with the arm abducted at 90°.-For the trapezius (upper, middle, lower), shoulder shrug, scapular retraction, and scapular depression will be tested, respectively, while sitting.-For the latissimus dorsi, isometric shoulder extension will be performed against resistance with the arm extended backward.

Temporal synchronization between motion and EMG data will be achieved using a TTL signal transmitted via the motion system’s analog trigger module, ensuring signal alignment across both systems. Each participant will complete propulsion trials in both modes, and three successful propulsion cycles will be recorded per condition for analysis.

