### 2.7. Data Analysis

All collected data will be analyzed using SPSS Statistics software (version 26.0, IBM Corp., Armonk, NY, USA). Descriptive statistics (mean ± standard deviation) will be used to summarize participant characteristics and all outcome measures.

To assess the normality of the data distribution, the Shapiro–Wilk test will be conducted. Based on these results, either parametric or non-parametric tests will be used. For normally distributed data, repeated-measures analysis of variance (ANOVA) will be conducted to compare biomechanical parameters (e.g., joint angles, ROM, iEMG, RMS values) between the two propulsion modes (push vs. pull). Mauchly’s test will be performed to assess the assumption of sphericity, and if violated, the Greenhouse–Geisser correction will be applied. Signals will be sampled at 2000 Hz.

For non-normally distributed variables, the Wilcoxon signed-rank test will be applied. All statistical analyses will adopt a two-tailed significance level of *p* < 0.05. To assess the magnitude of differences between conditions, effect sizes will be reported (Cohen’s d or partial eta squared, as appropriate).

Additionally, kinematic variables such as shoulder flexion and extension angles, as well as stroke cadence, will be calculated over complete propulsion cycles. EMG signals will be band-pass filtered (20–450 Hz), full-wave rectified, and smoothed using the root mean square (RMS) method with a 100-ms moving window. Integrated EMG (iEMG) data will also be computed to capture the total muscle activation over each propulsion cycle. EMG data will be normalized to maximum voluntary contraction (%MVC). Comparisons of muscle activity patterns will be made across propulsion modes to evaluate biomechanical efficiency, with a focus on reduced activation in shoulder prime movers during the pull phase.

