Beyond the magnitude of force, the direction and pattern of muscle recruitment during propulsion play a key role in injury prevention. Reverse propulsion studies have demonstrated favorable changes in muscle activation patterns—specifically, reduced strain on frequently overused anterior muscles such as the deltoid and pectoralis major and increased activation of posterior muscles like the trapezius and latissimus dorsi [11,23]. In another study, Jahanian et al. examined a geared wheelchair wheel design and found that it reduced shoulder joint forces during propulsion under high-resistance conditions, such as ramp ascent [24]. The dual-propulsion system proposed in this protocol incorporates both forward and backward propulsion, which is hypothesized to shift the muscular workload across phases of movement dynamically. This redistribution may help lower the cumulative load on any single muscle group and improve long-term shoulder health among users.

However, the advantages of pull propulsion are not consistent across all device designs. For example, Rocha et al. reported that although novel geared wheelchair wheels reduced the number of propulsion strokes required, novice users exhibited higher energy expenditure and perceived exertion compared to those using traditional handrim wheels [25]. These mixed findings emphasize the need for device-specific biomechanical evaluations. In contrast to rowing-style systems, our device employs a direct push–pull lever mechanism that minimizes frictional losses and supports natural upper limb motion throughout both propulsion phases. Furthermore, our protocol includes a structured orientation and practice period designed to mitigate novelty-related effects and enable participants to become biomechanically accustomed to the dual-propulsion system.

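### Primary iEMG is totalled per propulsion cycle with no scaling to time or distance, so a handrim-versus-lever comparison can reflect stroke length rather than muscular demand, in either direction

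*Protocol article*

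**What the plan says.** Section 2.5 (Outcome Measures) states: "Normalized iEMG and RMS values will serve as the primary metrics for inter-condition comparison". Section 2.6 (Procedures) explains that "iEMG will reflect the cumulative muscle activity over time", and section 2.7 (Data Analysis) sets the integration window: "Integrated EMG (iEMG) data will also be computed to capture the total muscle activation over each propulsion cycle". Sections 2.5, 2.6 and 2.7 all normalise EMG to MVC; no other scaling is mentioned.

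The analysis uses a fixed count of cycles: "three successful propulsion cycles will be recorded per condition for analysis" (section 2.6). The task itself is a fixed distance: "Each propulsion condition will be completed five times over a 10-m track" (section 2.4). The two conditions are conventional handrim pushing (section 2.2) and pulling on levers that drive the wheels through gears (section 2.3). Stroke cadence is to be computed, but the article does not use it to scale iEMG.

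Section 2.7 also says how the result will be read: "Comparisons of muscle activity patterns will be made across propulsion modes to evaluate biomechanical efficiency", with attention to lower activation of the main shoulder muscles when pulling.

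**The concern.** An integral over a cycle is mean amplitude times cycle duration. If the two drives produce cycles of different length, iEMG per cycle differs between modes even when the muscles work equally hard. It also ignores how many cycles are needed to cover the track.

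This matters because the article's rationale concerns cumulative load from repetition (Introduction and Discussion), and because the between-mode comparison is to be read as efficiency. A difference in stroke length could then be reported as a difference in muscular demand. The article's own Discussion shows that stroke count and effort can separate: it cites geared wheels that "reduced the number of propulsion strokes required" while novice users spent more energy.

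**Working it through.** The article gives no cadence, speed, gear ratio or SD, so it has no figure to reproduce. All values below are assumptions, shown as a range.

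**Formulas.** Take pull/push ratios: a = mean amplitude (%MVC), t = cycle duration, d = distance per cycle.

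- iEMG per cycle: a × t
- Number of cycles over the same track: 1/d
- iEMG over 10 m: a × t / d
- Speed: v = d / t, so iEMG over 10 m is also a / v

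The two measures have opposite signs when d < a·t < 1 (per cycle flatters the device) or 1 < a·t < d (per cycle penalises it). At equal speed (t = d) these become 1 < a < 1/d and 1/d < a < 1.

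**Equal speed, t = d.**

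| a | t = d | Per cycle (a·t) | Per 10 m (a·t/d) |
|---|---|---|---|
| 1.10 | 0.70 | 0.77 | 1.10 |
| 1.10 | 0.80 | 0.88 | 1.10 |
| 1.10 | 0.90 | 0.99 | 1.10 |
| 0.90 | 1.20 | 1.08 | 0.90 |
| 0.90 | 1.30 | 1.17 | 0.90 |

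In the second row the device looks 12% better per cycle but needs 10% more activation over the track. In the last row it looks 17% worse but needs 10% less.

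**Would 30 participants turn this into a significant result?** A simulation of 20,000 runs used a two-sided 5% paired t-test on the log ratio. With two modes, the planned repeated-measures ANOVA is the same kind of paired comparison. It assumed n = 30, equal speed, the same d for everyone, and a within-person log-ratio SD of 0.2, 0.3 or 0.4.

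| a, d | Per-cycle test significant | SD 0.2 | SD 0.3 | SD 0.4 | Per-10-m test significant in the same direction |
|---|---|---|---|---|---|
| 1.00, 0.90 | for the device | 79.7% | 45.7% | 28.4% | about 2.5% |
| 1.00, 0.80 | for the device | 100% | 97.6% | 83.7% | about 2.5% |
| 1.10, 0.90 | for the device | 4.7% | 3.7% | 3.3% | at most 0.1% |
| 1.10, 0.80 | for the device | 92.5% | 62.2% | 39.2% | at most 0.1% |
| 0.90, 1.30 | against the device | 98.5% | 79.0% | 55.0% | 0.0% |

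**What is not affected.** Within one mode every muscle is integrated over the same cycle. A muscle's share is (its amplitude × T) / (sum of amplitudes × T), and T cancels. Balance between muscles therefore does not depend on cycle duration.

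**Limit of a per-distance measure.** Because iEMG per 10 m equals a / v, it moves with speed. With a = 1, t = 0.8 and d = 0.7, it is 0.8/0.7 = 1.14. Speed is then 0.7/0.8 = 0.875, so the whole 14% excess comes from pulling 12.5% more slowly, not from greater amplitude.

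**The case against.** A reader might infer that the metric is tilted towards the device. The documents do not support that. The only stroke-count evidence they cite is a different geared product that needed fewer strokes. Over a fixed distance that means more distance per stroke and, at similar speed, longer cycles, which would count against a device. The direction is open.

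A reader might also take unequal cycles as established. They are not: different interfaces, gearing and an apparently free cadence make them likely, but no value is given. Nor is the lack of a stated pacing rule a fault in itself, since an article may leave it to the full protocol. Pacing by speed alone would not help in any case, as the reversals above occur at equal speed. Only matching cadence as well would remove them.

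Four further objections deserve weight.

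- **RMS is also primary and does not grow with duration.** At equal speed the per-distance ratio is simply the amplitude ratio, so a gap between iEMG and RMS, read with cadence, would expose a duration effect. This lowers the severity. It does not remove the problem, because iEMG has equal standing as a primary metric.
- **The hypothesis in section 2.2 is partly about balance,** which is unaffected. Its other part, lower shoulder loading, and the efficiency reading in section 2.7 are exposed wherever they rest on absolute iEMG compared between modes.
- **Activation per stroke is a legitimate quantity** for overuse research. It is, but it is not efficiency over a distance.
- **Normalised might mean that cycles are stretched to a common length.** The article ties the normalisation to MVC and describes iEMG as accumulating over time, so that reading does not fit its text.

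**Conclusion.** The point stands with bounded scope. As defined, absolute per-cycle iEMG mixes cycle duration and distance per cycle with muscular demand, so it can mislead in either direction when compared between handrim and lever and read as efficiency. Under assumed equal-speed ratios it can show 0.88 where activation over the track is 1.10, or 1.17 where it is 0.90. The size in this trial is unknown, because it depends on cycle durations and stroke distances that the article does not give.

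The conclusion covers absolute iEMG between modes only, not between-muscle balance or RMS. Since the EMG recordings and cadence are already planned, the repair lies in the analysis and not the design. It should be fixed before analysis, but it does not invalidate the study.

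**What to change.** In section 2.7:

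1. Base the between-mode efficiency comparison on iEMG per distance: integrate %MVC over the 10 m, or multiply mean per-cycle iEMG by the number of strokes, and divide by 10 m.
2. Show it beside time-normalised mean amplitude (RMS, %MVC).
3. Report cycle duration, cadence and mean speed by mode.
4. Add a speed-adjusted sensitivity analysis, because per-distance iEMG still depends on speed.
5. Describe per-cycle iEMG only as activation per stroke, not as efficiency.

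Distance should come from the track length and the stroke count. The markers named in section 2.6 are on the shoulder, elbow, wrist and hand, which move relative to the chair and are a poor source for distance per cycle.

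The cost is a few lines of text, a stroke count and time for each 10-m run, and a little more processing. No extra participants or trials are needed. Multiplying by the stroke count assumes that the three analysed cycles represent the whole run; integrating over the full 10 m avoids that assumption.

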## 3. Discussion

This protocol outlines a structured approach to evaluating the usability and biomechanical performance of a novel detachable dual-propulsion device for manual wheelchair users. It incorporates synchronized 3D motion capture and surface electromyography (EMG) to analyze upper limb movement and muscle activity. By employing a within-subjects design, the study is structured to enable direct comparisons between push and pull propulsion conditions under controlled laboratory settings. While this approach facilitates individual-level comparisons, appropriate statistical methods (parametric or non-parametric) will be applied based on the distribution of collected data [19,20].

Previous studies have reported that repetitive pushrim propulsion generates cumulative strain on upper limb joints—especially the shoulder complex—resulting in high rates of rotator cuff injuries, shoulder impingement, and chronic overuse conditions among long-term manual wheelchair users [1,3,21]. To address these concerns, alternative propulsion systems such as lever-driven mechanisms and reverse propulsion have been explored to help redistribute mechanical load and reduce the risk of upper limb injury. For example, lever-based systems have demonstrated effectiveness in reducing peak handrim forces and joint loading by offering a mechanical advantage through longer moment arms and more continuous force application during propulsion [6,22].

Recent studies on push–pull lever propulsion systems have shown that combining forward pushing and backward pulling enhances propulsion efficiency while distributing muscular demand more evenly between anterior and posterior upper limb muscles [7]. For instance, le Rütte et al. reported that a centrally mounted push–pull lever system significantly reduced peak propulsion forces and energy expenditure compared to traditional handrim propulsion, while also promoting smoother force application and a lower perception of strain [7]. These findings provide empirical support for the rationale behind our device design, which incorporates push–pull mechanics in a detachable form that can be retrofitted to existing manual wheelchairs.

Beyond the magnitude of force, the direction and pattern of muscle recruitment during propulsion play a key role in injury prevention. Reverse propulsion studies have demonstrated favorable changes in muscle activation patterns—specifically, reduced strain on frequently overused anterior muscles such as the deltoid and pectoralis major and increased activation of posterior muscles like the trapezius and latissimus dorsi [11,23]. In another study, Jahanian et al. examined a geared wheelchair wheel design and found that it reduced shoulder joint forces during propulsion under high-resistance conditions, such as ramp ascent [24]. The dual-propulsion system proposed in this protocol incorporates both forward and backward propulsion, which is hypothesized to shift the muscular workload across phases of movement dynamically. This redistribution may help lower the cumulative load on any single muscle group and improve long-term shoulder health among users.

However, the advantages of pull propulsion are not consistent across all device designs. For example, Rocha et al. reported that although novel geared wheelchair wheels reduced the number of propulsion strokes required, novice users exhibited higher energy expenditure and perceived exertion compared to those using traditional handrim wheels [25]. These mixed findings emphasize the need for device-specific biomechanical evaluations. In contrast to rowing-style systems, our device employs a direct push–pull lever mechanism that minimizes frictional losses and supports natural upper limb motion throughout both propulsion phases. Furthermore, our protocol includes a structured orientation and practice period designed to mitigate novelty-related effects and enable participants to become biomechanically accustomed to the dual-propulsion system.

From an injury prevention perspective, distributing propulsion effort between the push and pull phases may reduce the repetitive overuse of anterior shoulder structures—such as the pectoralis major and supraspinatus—which are frequently involved in propulsion-related pathologies [3,4]. Supporting this rationale, Mulroy et al. [26] analyzed shoulder muscle activity in individuals with paraplegia during wheelchair propulsion. They observed distinct differences in electromyographic patterns between the push and recovery phases, with significantly elevated loads on anterior musculature, particularly during push strokes. Such findings suggest that propulsion strategies that distribute muscular workload more evenly across different phases of motion may reduce fatigue and help prevent long-term musculoskeletal injuries. In line with this, our dual-propulsion system is designed to lower peak kinetic loads and balance activation across muscle groups. If confirmed using EMG and kinematic analyses, these effects may contribute to reducing the risk of shoulder overuse injuries among manual wheelchair users.

Usability is another crucial factor influencing the adoption of new propulsion technologies. Cowan et al. [27] demonstrated that heavier wheelchair configurations increase propulsion force requirements, especially in older adults with limited upper body strength. These findings underscore the importance of lightweight and user-centered design in assistive mobility devices.

The current dual-propulsion device was specifically developed to address these issues. Its detachable and lightweight structure is intended to improve portability, while the intuitive push–pull mechanism enhances ease of use, especially for novice users. These characteristics aim to reduce the physical burden of propulsion and make the system more accessible to a broader range of manual wheelchair users.

Beyond usability, this study emphasizes the integration of objective biomechanical performance measures in the evaluation of assistive devices. Following the recommendation by Dittli et al. [13], the protocol includes synchronized motion capture and surface EMG to quantify propulsion mechanics and muscular engagement across propulsion modes.

By adopting a structured biomechanical evaluation framework, the study builds upon existing knowledge in wheelchair propulsion and expands it using a novel dual-propulsion design. This evidence-based engineering and clinical approach strikes a balance between innovation and practical feasibility. If our findings confirm the expected benefits—namely, lower peak shoulder loading and more symmetrical muscle activation—this study may provide meaningful contributions to both assistive technology development and rehabilitation science, while also offering evidence supporting the applicability of dual-propulsion in real-world settings.

